### Endpoints

The primary endpoint is time-to-full recovery within a follow-up period of 6 months. Full recovery is defined by the following criteria: discharged from the hospital (out-patient), normal diet (defined by tolerating solid food and more than 1L of fluid orally), temperature < 38.0°C, and VAS pain score < 4, no use of daily pain medication or back to pre-illness pain medication use, and resuming to pre-illness working activities; as assessed by questionnaires and out-patient clinic visits.

The secondary endpoints are: proportion of patients who develop complicated diverticulitis require surgery or non-surgical intervention; number of days outside the hospital in a 6 months period; direct and indirect medical costs at 6 months follow-up; occurrence of complicated diverticulitis defined as abscess, perforation, stricture and/or fistula; predefined side-effects of initial antibiotic treatment (e.g. antibiotic resistance/sensitivity pattern, allergy); morbidity (e.g. pneumonia, myocardial infarction, urinary tract infection); mortality; readmission rate within 6 months and acute diverticulitis recurrence rates at 12 and 24 months follow-up. Changes in health status and valuation over time will be measured using generic and disease specific quality of life questionnaires (Euro-Qol 5D, Short Form 36 (SF-36) and the Gastro-Intestinal Quality of Life Index (Giqli)) on admission and after 3, 6, 12 and 24 months.

A recurrence is defined as ultrasound- or CT-proven acute diverticulitis after complete resolution of symptoms more than 1 month after initial discharge from hospital. If a patient dies during follow-up, the reason for death will be recorded as related or unrelated to diverticular disease.

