### Sample size calculation and date analysis

A non-inferiority design was chosen. Time-to-full recovery in the liberal strategy arm must not exceed a clinically relevant difference of more than 5 days compared with the conservative strategy. When this condition is fulfilled, the potential advantages of the liberal (non-antibiotic) strategy become dominant: patient well being when the need of hospital admission can be avoided, less costs, less antibiotic resistance and less other side effects. The study must have the power (superiority) to detect a difference in time-to-full recovery of 5 days.

The median time-to-full recovery is 21 days based on the National Dutch Hospital Registry data with an average of 7 days admission and an assumed additional median 14-day out-patient period to full recovery. To reject the null-hypothesis of a difference in time-to-full recovery of 5 days or less, using a time-to-event analysis with a power of 85% at a confidence level of 95%, an accrual period of 730 days and a follow-up period of 180 days, at least 264 patients need to be included in each treatment arm. With an estimated one percent of the trial patients lost to follow-up, a total 533 patients is needed.

The primary endpoint is time-to-full recovery. Kaplan-Meier curves depicting the proportion of patients with full recovery since randomisation will be constructed for both strategies. The log rank test will be used to test for superiority of one strategy compared with the other. Testing for non-inferiority will be done by calculating the hazard ratio for the liberal strategy compared with the conservative strategy using Cox regression. We will calculate a one-sided 95% confidence interval for this ratio to determine whether it reaches outside the hazard ratio belonging to an equivalence limit of a difference of 5 days in median survival time.

For other endpoints data will be compared by the Student's t test, Wilcoxon rank sum test, Chi square test or Fischer exact test as appropriate. In superiority tests a two-tailed P value ≤ 0.05 will be considered statistically significant, whereas one-sided tests will be performed in non-inferiority testing. The main analyses will be based on the intention to treat principle. Predefined subgroup analyses to investigate whether treatment effects are different in subgroups will be performed for Hinchey classification 1a versus 1b and for participating center.

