### Economic evaluation

The economic evaluation will be performed from a societal perspective as a cost-effectiveness and cost-utility analysis. The main analyses include costs per day reduction to achieve full recovery and costs per QALY gained. Additional sensitivity analyses, regarding differences in possible subgroups, will be performed.

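### Quality of life has a baseline and four follow-up scores, but the only tests named for it are unadjusted two-sample tests, which are valid but lose precision

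*Protocol article*

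**What the plan says.** Under Endpoints, the protocol article states: "Changes in health status and valuation over time will be measured using generic and disease specific quality of life questionnaires". The instruments are EQ-5D, SF-36 and GIQLI, completed "on admission and after 3, 6, 12 and 24 months". Under Objective, patient well-being is named as a secondary outcome.

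Under Sample size calculation and date analysis, a single sentence covers every non-primary endpoint: "data will be compared by the Student's t test, Wilcoxon rank sum test, Chi square test or Fischer exact test as appropriate". The significance rule follows: "In superiority tests a two-tailed P value ≤ 0.05 will be considered statistically significant". The section does not say whether the follow-up score or the change from baseline is compared, or whether each visit is tested separately. It does name a regression model, Cox, for the primary endpoint.

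Under Economic evaluation: "The main analyses include costs per day reduction to achieve full recovery and costs per QALY gained". That section gives no QALY formula, horizon, test or adjustment, and does not refer back to the tests above.

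**The concern.** This is a stated choice of method, not a gap left for a later plan. Read naturally, the words about appropriateness select among the four listed tests by type of data. They do not add a longitudinal model. Quality of life falls under this sentence, so a design with one baseline and four follow-ups would be analysed as independent two-group comparisons.

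The baseline is taken during acute illness, so its correlation with scores months later may be low. In that setting a change score, which the article's own wording about change over time suggests, can be noisier than the follow-up score alone. At stake is the width of the intervals for a named secondary outcome. Those intervals will be read when judging whether patients fare as well without antibiotics.

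**Working it through.** **Inputs.** The plan gives n: "at least 264 patients need to be included in each treatment arm". That figure was set for the primary endpoint and is used here only as n = 264. The plan gives no precision or power figure for quality of life, so there is none to reproduce. It also gives no correlations or standard deviations. Assumed: correlation r between baseline and follow-up of 0.2 to 0.5, and a ratio k of baseline SD to follow-up SD of 1.

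**Formulas.** The variance of the difference between arms at one visit is (2 × SD² / n) × f, where SD is the follow-up SD and f is
- follow-up score alone: 1
- change score: 1 + k² − 2kr, which is 2(1 − r) when k = 1
- baseline-adjusted: 1 − r²

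**Results for k = 1.**

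| r | f, follow-up | f, change | f, adjusted | adjusted / follow-up | adjusted / change |
|---|---|---|---|---|---|
| 0.2 | 1 | 1.60 | 0.96 | 96% | 60% |
| 0.5 | 1 | 1.00 | 0.75 | 75% | 75% |

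**In standard errors.** √(2/264) = 0.087 SD for the follow-up score. Multiplying by √f gives 0.110 (r = 0.2) and 0.087 (r = 0.5) for the change score, and 0.085 and 0.075 for the adjusted analysis.

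**In patients.** An adjusted analysis needs 264 × 0.96 = 253 or 264 × 0.75 = 198 per arm to match 264 with the follow-up score. To match 264 with the change score it needs 264 × 0.60 = 158 or 264 × 0.75 = 198.

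**Sensitivity.** At r = 0.7 and k = 1, f is 1, 0.60 and 0.51, so the ratios are 51% (follow-up) and 85% (change). If the acute-phase SD were 1.5 times the follow-up SD, f for the change score would be 3.25 − 3r, that is 2.65 or 1.75. The ratio to the change score would then be 0.96/2.65 = 36% or 0.75/1.75 = 43%. This last case applies only if change scores are tested and the SD ratio is as assumed. The article documents neither.

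**Validity.** In 4,000 simulated trials under no effect at each of r = 0.3, 0.5 and 0.7, with 264 per arm, the rejection rate at the 5% level was 4.2% to 5.5%. This held for the follow-up t test, the change-score t test, the Wilcoxon test and the adjusted analysis alike.

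**QALY, conditional.** Suppose QALYs were computed by linear interpolation over 0, 3 and 6 months and compared unadjusted. The weights would be 0.125, 0.25 and 0.125 year, so baseline carries 0.125/0.5 = 25%. With equal SDs and all correlations equal to r, the QALY variance in SD² units is 0.09375 + 0.15625r. Its covariance with baseline is 0.125 + 0.375r. At r = 0.2 the share explained by baseline is 0.20²/0.125 = 32%, so adjustment cuts the standard error by 1 − √0.68 = 18%. At r = 0.5 the share is 0.3125²/0.1719 = 57% and the cut is 34%.

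**The case against.** The strongest reply is that one generic sentence in a condensed article summarises valid tests on randomised arms, and that a mixed model is a refinement. Validity is conceded: the arms are comparable by design and the interval already allows for chance imbalance. At the low correlations that acute illness makes plausible, the gain over the follow-up score alone is also small, only 4% of the variance at r = 0.2. What stands is that the article names a method, and that one of its two possible readings is clearly inefficient at those same low correlations.

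Some stronger readings are tempting but not supported:
- *The plan throws the baseline away.* That is true only if the follow-up score is tested. A test on change scores uses the baseline, though inefficiently, and the article does not say which is meant.
- *Chance baseline differences will drive the QALY result.* The sentence on tests does not govern the economic evaluation, which states no QALY method. Even unadjusted, the effect would be added noise, not bias. Setting that noise against the QALY value of a 5-day delay needs an assumed utility loss, and the article never uses its margin that way.
- *Twelve tests give a 46% chance of a false positive.* The figure 1 − 0.95¹² requires twelve independent tests. Scores on overlapping instruments in the same patients are correlated, and testing each visit separately is not stated.

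A fair caution also stands. The article does not place the first questionnaire before randomisation, so a usable baseline cannot be taken for granted.

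**Conclusion.** The point holds as a matter of efficiency. The tests named for quality of life are valid but make poor use of one baseline and four follow-up scores. Under an assumed correlation of 0.2 to 0.5, baseline adjustment brings the variance to 75-96% of that of the follow-up score. With equal SDs it brings it to 60-75% of that of the change score. The size depends on correlations and SDs that the article does not give, and on which score is tested. The primary analysis is untouched and no bias is shown. The QALY part is advice for whatever method is adopted and not an error in the text. The sponsor should make the change because it improves precision on a named secondary outcome at almost no cost.

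**What to change.** Under Sample size calculation and date analysis, take the quality-of-life scores out of the generic sentence. Analyse each with one mixed model for repeated measures. The outcome is the score at 3, 6, 12 and 24 months, and the terms are treatment, visit, treatment by visit, and baseline score by visit. Give one joint treatment test per score, with visit-specific differences and intervals as description.

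Define the baseline as a score taken at or before randomisation. The present wording, on admission, does not fit liberal-arm patients who are never admitted. Because neither patients nor physicians are blinded, a score taken after allocation could be coloured by it.

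Under Economic evaluation, whatever QALY method is adopted, estimate the incremental QALYs with adjustment for baseline EQ-5D utility.

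Cost: analysis wording, with no additional patients or visits. It needs no new data if the first questionnaire is already completed before allocation. If it is not, its timing must be fixed as well.

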### Cost analysis

All related costs will be estimated based on the actual input terms of resource use and personnel in the 6-month follow-up period after randomization. For all cost-items such as hospital admission, medication used, diagnostic tests, unit costs will be derived from the Dutch costing manual or determined in cooperation with the hospital administration. Direct medical costs will be recorded in the case record forms. Indirect costs arising from losses in productivity will be assessed by means of the Health and Labor questionnaire and will be calculated by means of the friction cost method.

### Economic evaluation

The economic evaluation will be performed from a societal perspective as a cost-effectiveness and cost-utility analysis. The main analyses include costs per day reduction to achieve full recovery and costs per QALY gained. Additional sensitivity analyses, regarding differences in possible subgroups, will be performed.

### Safety monitoring

Adverse events are defined as any undesirable experience occurring to a subject during a clinical trial, whether or not considered related to the investigational drug. All adverse events reported spontaneously by the subject or observed by the investigator or his staff will be recorded. A serious adverse event (SAE) is any untoward medical occurrence or effect that at any dose results in death; is life threatening (at the time of the event); requires hospitalization or prolongation of existing inpatients' hospitalization; results in persistent or significant disability or incapacity; is a congenital anomaly or birth defect; is a new event of the trial likely to affect the safety of the subjects, such as an unexpected outcome of an adverse reaction, major safety finding from a newly completed animal study, etc. All SAEs will be reported to the accredited Medical Ethical Committee (MEC) that approved the protocol, according to the requirements of that MEC.

Suspected unexpected serious adverse reactions (SUSAR) are all untoward and unintended responses to an investigational product related to any dose administered.

Unexpected adverse reactions are adverse reactions, of which the nature, or severity, is not consistent with the applicable product information.

The sponsor will report expedited the following SUSARs to the MEC; SUSARs that have arisen in the clinical trial that was assessed by the MEC; SUSARs that have arisen in other clinical trial of the same sponsor and with the same medicinal product, and that could have consequences for the safety of the subjects involved in the clinical trial that was assessed by the MEC. The remaining SUSARs are recorded in an overview list (line-listing) that will be submitted once every half year to the MEC. This line listing provides an overview of all SUSARs from the study medicine, accompanied by a brief report highlighting the main points of concern.

The sponsor will report expedited all SUSARs to the competent authority, the Medicine Evaluation Board and the competent authorities in other Member States. The expedited reporting will occur not later than 15 days after the sponsor has first knowledge of the adverse reactions. For fatal or life threatening cases the term will be maximal 7 days for a preliminary report with another 8 days for completion of the report. There is no need to break any code in case of a SUSAR because due to the nature of the study in which neither participant nor treating physician are blinded.

In addition to the expedited reporting of SUSARs, the sponsor will submit, once a year throughout the clinical trial, a safety report to the accredited MEC, competent authority, Medicine Evaluation Board and competent authorities of the concerned Member States. This safety report consists of: a list of all suspected (unexpected or expected) serious adverse reactions, along with an aggregated summary table of all reported serious adverse reactions, ordered by organ system, per study; a report concerning the safety of the subjects, consisting of a complete safety analysis and an evaluation of the balance between the efficacy and the harmfulness of the medicine under investigation.

An independent data and safety monitoring committee will evaluate the progress of the trial and will examine safety parameters at regular intervals (every 25 patients). The committee can unblind the data whenever deemed necessary based on reported adverse events. All involved physicians will repetitively be asked to report any potential adverse events caused by the study protocol. These adverse events will be listed and discussed with the monitoring committee. The monitoring committee can ask for a full report in order to discuss a specific adverse event. A copy of this report will be send to the central ethics board and to the involved physicians. All deceased patients will be evaluated by the safety committee for cause of death and possible trial related serious adverse effects. Every death will be reported to the central ethics board and the local ethics board. The Data Safety Monitoring Board will consist of an epidemiologist/statistician who is the chairman, an independent surgeon and an independent radiologist.

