### Study outline

Patients will be randomly allocated to one of the following two treatment strategies: Conservative strategy including immediate antibiotic treatment or liberal strategy without antibiotics (supportive measures only). (Table 4).

**Table 4 T4:** Treatment strategies

Conservative strategy with antibiotics	Liberal strategy without antibiotics
- Hospital admission;	- Admission only if discharge criteria are not met;

- Intravenous fluids and at least 48 hours of intravenous antibiotics and subsequently switch to oral antibiotics if tolerated (otherwise continuation i.v.) to complete a full 10-day treatment duration;	- No initial antibiotics;

- Adequate pain relief (VAS < 4);	- Adequate pain relief (VAS < 4);

- Oral intake as tolerated;	- Oral intake as tolerated;

- Daily monitoring.	- Daily monitoring when admitted to the hospital;

-Self monitoring at home after discharge -Out patient follow-up at regular intervals	- Self monitoring at home. - Out patient follow-up at regular intervals

In the conservative strategy, the use of antibiotics will be intravenously for at least 48 hours after which route of administration can be switched to orally if tolerated. Hospital admission in the liberal strategy is needed for patients with nausea and vomiting, in need of intravenous fluids or for patients with excessive pain not properly reacting to oral pain medication.

The interval between start of symptoms of the patient and administration of antibiotics will be registered. Also the period after inclusion and the actual first administration of antibiotics will be registered.

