In both strategies CT is repeated in case of clinical deterioration. For patients in the liberal strategy treatment arm, clinical deterioration and/or proven subsequent complicated diverticulitis and/or other infectious foci (e.g., pneumonia, infections) may dictate start of antibiotic treatment, instigated by the treating physician. Criteria to start antibiotics in the liberal arm are temperature > 39°C, positive blood cultures and clinical suspicion of bacteraemia (i.e. sepsis). Criteria for sepsis are set by the American College of Chest Physicians and the Society of Critical Care Medicine. Two or more symptoms are required: Body temperature < 36°C or > 38°C, heart rate higher than 100 beats a minute, respiratory rate higher than 20 breaths a minute and white blood cell count < 4 × 10^9 ^or > 12 × 10^9 ^cells/L [31]. Also another infectious focus (e.g., pneumonia, urinary tract infections) may dictate start of antibiotic treatment, instigated by the treating physician.

The following discharge criteria are applied in both strategies: normal diet (defined by tolerating solid food and more than 1L of fluid orally), temperature < 38.0°C, VAS (Visual Analoge Score) pain score < 4 (with paracetamol only), self support as compared to the pre-illness level, and acceptance by the patient.

All outpatients will daily monitor and register their body temperature. Written and oral instructions at discharge are given, and relevant telephone numbers and contact information will be provided. In case of fever above 38˚C, progression of pain above a VAS of 4 or other clinical signs of deterioration, patients can contact the hospital or emergency department immediately.

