### Randomization

Computerized block randomization for allocation of treatment group, stratified for center and for Hinchey 1a and 1b, will take place after all inclusion and exclusion criteria have been verified and informed consent has been obtained. A standardized case record from (CRF) will be used. This CRF is partially web-based via a secured internet module. A minimum of 10% of the CRF data will be verified with source data by an independent audit.

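### Adverse events are recorded when volunteered or observed, and early observation depends on the allocated arm, so mild untreated events may be ascertained unequally (minor, cheap to fix)

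*Protocol article*

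**What the plan says.** Safety monitoring states the collection rule: "All adverse events reported spontaneously by the subject or observed by the investigator or his staff will be recorded". The same section confirms that patients and treating physicians are unblinded.

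Table 4 (Study outline) sets the early contact. Conservative patients are admitted and monitored daily. For liberal patients it says "Admission only if discharge criteria are not met" and "Daily monitoring when admitted to the hospital"; otherwise they monitor themselves at home. The conservative arm receives at least 48 hours of intravenous antibiotics and may then switch to oral treatment (Study outline), for a 10-day course (Antibiotics).

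Other provisions bear on ascertainment:

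- Both arms have "Out patient follow-up at regular intervals" (Table 4), and recovery is assessed by questionnaires and clinic visits (Endpoints).
- Outpatients record their temperature daily and receive instructions; "relevant telephone numbers and contact information will be provided" (Study outline).
- A newly found allergy leads to a change of antibiotic (Antibiotics).
- "A standardized case record from (CRF) will be used" (Randomization), and "Direct medical costs will be recorded in the case record forms" (Cost analysis).
- "All involved physicians will repetitively be asked to report any potential adverse events caused by the study protocol" (Safety monitoring).

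Morbidity and predefined side-effects of the initial antibiotics are secondary endpoints (Endpoints). The sample size section counts fewer side effects among the advantages that carry weight once non-inferiority is shown.

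**The concern.** Both routes into the record, volunteering and observation, depend on contact with staff, and in the first days randomisation determines that contact. Two distortions can follow.

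1. A mild event in the early days is more likely to be seen in an admitted conservative patient than in a liberal patient at home. This inflates the conservative count and flatters the liberal strategy.
2. The antibiotic course continues after discharge. A mild rash or loose stools starting at home may never be mentioned. This lowers the conservative count almost alone, since liberal patients get no initial antibiotics, and so works against the liberal strategy.

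At stake is the between-arm comparison of mild morbidity and side-effects. It supports the argument for the liberal strategy but does not decide non-inferiority. The Discussion also says that the study addresses Clostridium-associated diarrhoea; a mild case that is never tested belongs to the exposed group.

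**Working it through.** The plan gives no figure to reproduce. The check has two parts: whether any stated provision equalises ascertainment, and how large the effect could be.

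**Provisions against the gap**

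- Clinic visits and recovery questionnaires reach both arms and are the strongest mitigation. The recovery criteria they are stated to assess are discharge, diet, temperature, pain, pain medication and return to work, not side-effects.
- The quality-of-life instruments are given on admission and from 3 months on, too late for events around day 10.
- Outpatients are told to call for fever, pain or deterioration. A mild rash or diarrhoea need not qualify.
- The drug switch and the cost records capture events that were recognised, treated or tested.
- The physician prompt is active, but it covers events attributed to the study protocol by unblinded physicians.

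What remains exposed is mild, untreated, untested events.

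**Size, early-observation mechanism (illustration)**

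From the document: 264 per arm. Assumed, because the document gives no values: a true mild-event rate of 10% in both arms (26.4 events each); e, the share of events in the initial-stay window; a, the share of liberal patients admitted; h, capture at home relative to capture in hospital.

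- Conservative capture = e + (1 − e)h
- Liberal capture = e[a + (1 − a)h] + (1 − e)h
- Difference = e(1 − a)(1 − h)

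With e = a = 0.5:

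| h | Capture, conservative vs liberal | Recorded events | Spurious reduction |
|---|---|---|---|
| 0.5 | 0.750 vs 0.625 | 19.8 vs 16.5 | 16.7% |
| 0.7 | 0.850 vs 0.775 | 22.4 vs 20.5 | 8.8% |
| 0.9 | 0.950 vs 0.925 | 25.1 vs 24.4 | 2.6% |

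Over e and a from 0.25 to 0.75 and h from 0.5 to 0.9, the reduction runs from 0.7% (0.2 events; e = 0.25, a = 0.75, h = 0.9) to 32.1% (7.4 events; e = 0.75, a = 0.25, h = 0.5).

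The standard error of the difference at 10% is √(2 × 0.1 × 0.9 / 264) = 2.61 points, or 6.9 events. The central gaps of 0.66 to 3.3 events are therefore 0.1 to 0.5 SE, and the extreme is 7.4/6.9 = 1.1 SE.

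If half of all events are treated or serious and fully captured in both arms, the reduction in all events is 1 − 0.8125/0.875 = 7.1% at h = 0.5 and 1 − 0.9625/0.975 = 1.3% at h = 0.9.

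If events instead fell evenly over the 180 days and the stay lasted 7 days, e = 7/180 = 0.04. With a = h = 0.5 the reduction is then 0.0097/0.519, about 2%.

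**Size, home-onset mechanism (illustration)**

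Background gives toxicodermia at 7–8% with amoxicillin: 264 × 0.07 = 18.5 to 264 × 0.08 = 21.1 cases. Between 2 days (minimum intravenous phase) and 7 days (average registry admission used in the sample size section) of the 10-day course fall in hospital. With even onset, 30–80% of cases start at home. With 10–50% of those missed, the missed share is 0.3 × 0.1 = 3% to 0.8 × 0.5 = 40%, or 18.5 × 0.03 = 0.6 to 21.1 × 0.40 = 8.4 cases. The upper end assumes that no case leads to care, so it is a ceiling.

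**The case against.** The strongest reply is that this is a journal article and the forms are not shown. The rule says that volunteered and observed events will all be recorded; it does not say that nothing else will be. The CRF or questionnaires may already ask about side-effects. This stands, and it is why the fix is conditional. It does not remove the point, because the article states a collection rule, and following that rule as written leaves early ascertainment dependent on allocation.

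It also stands that most named endpoints lead to care: pneumonia, myocardial infarction, urinary infection and recognised allergy would mostly be treated or lead to a drug change. No test or threshold in the sample size section depends on mild events. The difference in admission is deliberate in a pragmatic comparison of strategies, although that does not require events to be ascertained differently.

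A reader might infer more: that the safety comparison is biased towards the liberal strategy, that the primary endpoint is compromised, or that a falsely significant difference is likely. The documents do not support these. The two mechanisms oppose each other, and recovery is assessed by questionnaires and visits in both arms. A large false-positive risk needs detection gaps such as 90% versus 50%, which give about a 44% chance of a spurious p < 0.05 at a true 10% rate. That gap implies a 44% reduction, beyond even the 32% extreme above, and no passage suggests it.

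**Conclusion.** The point holds as a minor one. The stated rule, arm-dependent early contact and the open-label design together allow mild untreated events to be ascertained unequally, and mild antibiotic side-effects starting at home to be missed. Size and net direction cannot be determined from the documents. The illustrations rest on assumed event rates, timing, admission share and home capture; centrally, the early-observation gap is at most about half a standard error. That the two mechanisms oppose each other gives no assurance that they cancel, and the recorded data could not show whether they did. Conclusions on the primary endpoint, deaths and other serious events, treated infections, readmissions and complicated diverticulitis are little affected.

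**What to change.** Unless the forms already do so, add one short solicited checklist to the existing questionnaires and visit forms: diarrhoea, any C. difficile result, rash or allergy, and urinary or respiratory infection. Use it in both arms on the same days since randomisation, including one existing contact after day 10. Base the between-arm comparison of mild side-effects and morbidity on these answers. List spontaneously reported or observed mild events descriptively, and compare serious and treated events from all sources.

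The cost is a few items on existing forms, with no new tests or staff, and no new visit if a contact already falls after day 10. The downside is slightly longer forms and more minor events on record. Self-report in an open-label trial can still be coloured by knowledge of treatment; the checklist equalises the opportunity to report, not the patient's expectations.
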